### **5.2.3 Study drug preparation of durvalumab and tremelimumab**

Based on average body WT of 75 kg, a fixed dose of 750 mg Q2W durvalumab and 75 mg Q4W tremelimumab (equivalent to 1 mg/kg Q4W) will be administered.

#### **Preparation of durvalumab doses for administration with an IV bag**

The dose of durvalumab for administration must be prepared by the Investigator's or site's designated IP manager using aseptic technique. Total time from needle puncture of the durvalumab vial to the start of administration should not exceed:

- 24 hours at 2°C to 8°C (36°F to 46°F)
- 4 hours at room temperature

If in-use storage time exceeds these limits, a new dose must be prepared from new vials. Infusion solutions must be allowed to equilibrate to room temperature prior to commencement of administration.

No incompatibilities between durvalumab and polyvinylchloride or polyolefin IV bags have been observed. Dose of 750 mg durvalumab for patients >30 kg will be administered using an IV bag containing 0.9% (w/v) saline, with a final durvalumab concentration ranging from 1 to 20 mg/mL, and delivered through an IV administration set with a 0.2- or 0.22-µm in-line filter. Remove 30.0 mL of IV solution from the IV bag prior to addition of durvalumab. Next, 30.0 mL of durvalumab (ie, 1500 mg of durvalumab) is added to the IV bag such that final concentration is within 1 to 20 mg/mL (IV bag volumes 100 to 1000 mL). Mix the bag by gently inverting to ensure homogeneity of the dose in the bag.

Patient weight at baseline should be used for dosing calculations unless there is a ≥10% change in weight. Dosing day weight can be used for dosing calculations instead of baseline weight per institutional standard.

For patients <30kg, Calculate the dose volume of durvalumab and tremelimumab and number of vials needed for the subject to achieve the accurate dose.

Durvalumab will be administered at room temperature (approximately 25°C ) by controlled infusion via an infusion pump into a peripheral or central vein. Following preparation of durvalumab, the entire contents of the IV bag should be administered as an IV infusion over approximately 60 minutes (±5 minutes), using a 0.2, or 0.22-µm in-line filter. Less than 55 minutes is considered a deviation.

The IV line will be flushed with a volume of IV solution (0.9% [w/v] saline equal to the priming volume of the infusion set used after the contents of the IV bag are fully administered, or complete the infusion according to institutional policy to ensure the full dose is administered and document if the line was not flushed.

Standard infusion time is 1 hour. However, if there are interruptions during infusion, the total allowed time should not exceed 8 hours at room temperature. The table below summarizes time allowances and temperatures.

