| QLQ-C30 and QLQ-CR29                                                                                                                  | X                          |                                                  | X  |    |    |    | X  |    |    |
| Durvalumab (750 mg)                                                                                                                   |                            | X                                                | X  | X  | X  | X  | X  | X  | X  |
| Tremelimumab (75mg)                                                                                                                   |                            | X                                                |    | X  |    | X  |    | X  |    |
| FOLFOX administration                                                                                                                 |                            | X                                                | X  | X  | X  | X  | X  |    |    |

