#### **5.1.1 Formulation/packaging/storage**

##### **Durvalumab**

Durvalumab will be supplied by AstraZeneca as a 500-mg vial solution for infusion after dilution. The solution contains 50 mg/mL durvalumab, 26 mM histidine/histidine-hydrochloride, 275 mM trehalose dihydrate, and 0.02% (weight/volume) polysorbate 80; it has a pH of 6.0. The nominal fill volume is 10 mL. Investigational product vials are stored at 2°C to 8°C (36°F to 46°F) and must not be frozen. Durvalumab must be used within the individually assigned expiry date on the label.

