### **5.2 Dose and treatment regimens**

#### **5.2.1 Treatment regimens**

##### **Durvalumab + tremelimumab**

Patient will receive 750mg durvalumab via IV infusion q2w for up to 8 doses/cycles and 75 mg tremelimumab via IV infusion q4w for up to 4 doses/cycles, and then continue 750mg durvalumab q2w starting on Week 16 for up to 20 months (40 doses). Dosing outside the window should be discussed with the Study Physician. Tremelimumab will be administered first. Durvalumab infusion will start approximately 1 hour after the end of tremelimumab infusion. The duration will be approximately 1 hour for each infusion. A 1-hour observation period is required after the first infusion of durvalumab and tremelimumab. If no clinically significant infusion reactions are observed during or after the first cycle, subsequent infusion observation periods can be at the Investigator's discretion.

(suggested 30 minutes after each durvalumab and tremelimumab infusion). FOLFOX will be administered last and will be delivered as standard practice q2w.

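### Section 5.2.3 tells the pharmacy to put 1500 mg of durvalumab in the bag for a 750 mg dose, twice the ordered amount

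*Protocol*

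**What the plan says.** The ordered dose is consistent. Section 5.2.1 states "Patient will receive 750mg durvalumab via IV infusion q2w for up to 8 doses/cycles" and continues the same dose in maintenance. The synopsis, the assessment schedules, the design overview, the retreatment rules and the opening of Section 5.2.3 also give 750 mg every two weeks. No visit in the protocol calls for 1500 mg.

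Section 5.2.3 then gives the only step-by-step bag preparation for the fixed dose. It begins with the right dose: "Dose of 750 mg durvalumab for patients >30 kg will be administered using an IV bag". The steps that follow are:

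- a withdrawal of 30.0 mL of saline to make room for the drug
- the addition of the drug: "Next, 30.0 mL of durvalumab (ie, 1500 mg of durvalumab) is added to the IV bag"
- a check that the "final concentration is within 1 to 20 mg/mL (IV bag volumes 100 to 1000 mL" range is met
- the infusion: "Following preparation of durvalumab, the entire contents of the IV bag should be administered as an IV infusion"

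Nothing tells the preparer to split the bag, infuse half of it or discard any. Section 5.1.1 gives the strength: "The solution contains 50 mg/mL durvalumab", in vials with a nominal fill of 10 mL.

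The 1500 mg figure also appears in three places that are not preparation orders: a Q4W fixed dose mentioned in Section 1.4.2.4, the product list in Table 9 (Section 15.1), and the worked example in Appendix 3 (1.5 g, 30.0 mL, 3 vials).

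**The concern.** Within one set of steps, the stated dose and the volume to draw up differ by a factor of two, and the volume is what the preparer acts on. This is an operative figure in a patient-safety instruction.

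Section 6.2.3 says the triple combination has never been evaluated, and Step 1 judges its safety on nine patients over two cycles. If some bags were made with 30.0 mL, the toxicity seen would belong to a different durvalumab exposure from the one the protocol reports. Section 10.2.3.1 adds that there is no specific treatment for an overdose. It also defines overdose by reference to the Investigator's Brochure unless the protocol specifies otherwise, so a protocol line that itself says 1500 mg could blur recognition of the event.

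**Working it through.** **Inputs**

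- Ordered dose: 750 mg every two weeks (Sections 5.2.1 and 5.2.3)
- Strength 50 mg/mL, 10 mL per vial (Section 5.1.1)
- Volume removed and volume added: 30.0 mL each; whole bag infused (Section 5.2.3)
- Permitted final concentration 1 to 20 mg/mL, bags of 100 to 1000 mL (Section 5.2.3)
- Reference weight 75 kg (Section 5.2.3)

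**1. The protocol's own conversion.** Mass = volume × strength: 30.0 mL × 50 mg/mL = 1500 mg. The stated mass is reproduced, so volume and mass agree with each other and both disagree with the 750 mg dose.

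**2. The volume for the ordered dose.** The Appendix 3 flat-dose formula gives 0.75 × 1000 / 50 = 15.0 mL. Vials: 15.0 / 10 = 1.5, rounded up to 2. For the volume as written: 30.0 / 10 = 3 vials.

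**3. Size of the error.** 1500 / 750 = 2.0 per affected infusion.

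**4. Does the concentration check catch it?** Equal volumes are removed and added, so the bag volume does not change.

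| Drug in bag | 100 mL bag | 1000 mL bag |
|---|---|---|
| 1500 mg (as written) | 15 mg/mL | 1.5 mg/mL |
| 750 mg (as ordered) | 7.5 mg/mL | 0.75 mg/mL |

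The wrong dose lies within 1 to 20 mg/mL at both ends. The right dose falls below the minimum in a 1000 mL bag; its largest admissible bag is 750 mg / 1 mg/mL = 750 mL. The printed bag range therefore fits 1500 mg, not 750 mg.

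**5. Exposure at 75 kg if the step is repeated every two weeks.**

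- As ordered: 750 / 75 = 10 mg/kg per infusion, 20 mg/kg per four weeks
- As written: 1500 / 75 = 20 mg/kg per infusion, 40 mg/kg per four weeks

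The highest-rate regimens in Sections 1.1.2 and 1.3.1, per four weeks: 10 mg/kg every two weeks is 2 × 10 = 20; 15 mg/kg every three weeks is 15 × 4/3 = 20; 20 mg/kg every four weeks is 20.

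**6. Is tremelimumab affected?** No. Its step adds 3.8 mL, and 3.8 × 20 mg/mL = 76 mg for a 75 mg dose, which is rounding.

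**The case against.** The conflict is visible. The sentence spells out 1500 mg shortly after the heading dose of 750 mg, every order elsewhere is 750 mg, and the Appendix 3 formula gives the right volume for 0.75 g. Many pharmacists would stop and query it. This lowers the chance of harm but does not make the instruction correct: 15.0 mL is written nowhere, and the only flat-dose example repeats 30.0 mL.

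Safeguards exist. Section 5.2.5 has the monitor verify the dose dispensed to each subject, and Section 10.2.3.1 requires any overdose to be reported within 24 hours. These act after preparation, and a monitor checking against the preparation text could accept 1500 mg. It is fair that the protocol does not show these checks failed, so whether the safety data reflect 750 mg is an open question, not an established defect.

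Section 1.3.1 reports no rise in adverse events with higher durvalumab doses at constant tremelimumab, and a single 1500 mg infusion at 75 kg is the 20 mg/kg already given every four weeks. That tempers the likely consequence of an isolated error. It does not cover 20 mg/kg every two weeks, and those cohorts had no FOLFOX.

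The other 1500 mg mentions are rightly secondary. The Appendix 3 arithmetic is correct for its own example, and 1500 mg every four weeks is the same four-week total as the ordered regimen.

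**Conclusion.** The volume step in Section 5.2.3 is wrong as written and must be corrected. It specifies 2.0 times the ordered dose: 1500 mg against 750 mg, or 30.0 mL against 15.0 mL. This rests only on the protocol's stated strength, ordered dose and whole-bag infusion. The 40 mg/kg per four weeks figure further assumes a 75 kg patient and the step being followed at every two-weekly infusion. Carry-over from text for the 1500 mg Q4W regimen is a plausible origin, but that is inference. Whether any patient received the higher dose cannot be told from the protocol. This version is dated January 2020 and Section 13.4 expects the last visit by Q2 2020, so much of the dosing may already have taken place.

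**What to change.** In Section 5.2.3, change the removed volume to 15.0 mL and the added volume to 15.0 mL (750 mg, 2 vials), and reduce the upper bag volume from 1000 mL to 750 mL.

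Send a pharmacy notice to all sites. Review the accountability and dispensing records kept under Section 5.2.5 for the dose prepared at each infusion. Three vials instead of two would flag a 1500 mg preparation, but that section names dose, lot number and dates, not vial counts, so the flag may not be available everywhere. Read the safety data, Step 1 included, against the exposure actually given.

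As minor tidying, change the Appendix 3 example to 0.75 g, 15.0 mL and 2 vials, and align Table 9 and the Q4W mention in Section 1.4.2.4 with 750 mg every two weeks.

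The cost is two volumes, one mass and one bag limit in the text, a letter to pharmacies, and a review based mainly on existing records.

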**Durvalumab hold and infusion times**

|                                                              |                                                     |
|--------------------------------------------------------------|-----------------------------------------------------|
| Maximum time from needle puncture to start of administration | 4 hours at room temperature, 24 hours at 2°C to 8°C |
| Maximum time for IV bag infusion, including interruptions    | 8 hours at room temperature                         |

In the event that either preparation time or infusion time exceeds the time limits outlined in the table, a new dose must be prepared from new vials. Durvalumab does not contain preservatives, and any unused portion must be discarded.

**Preparation of tremelimumab doses for administration with an IV bag**

The dose of tremelimumab for administration must be prepared by the Investigator's or site's designated IP manager using aseptic technique. Total time from needle puncture of the tremelimumab vial to the start of administration should not exceed:

- 24 hours at 2°C to 8°C (36°F to 46°F)
- 4 hours at room temperature

It is recommended that the prepared final IV bag be stored in the dark at 2°C-8°C (36°F-46°F) until needed. If storage time exceeds these limits, a new dose must be prepared from new vials. The refrigerated infusion solutions in the prepared final IV bag should be equilibrated at room temperature for about 2 hours prior to administration. Tremelimumab does not contain preservatives and any unused portion must be discarded.

No incompatibilities between tremelimumab and polyvinylchloride or polyolefin IV bags have been observed. Doses of 75 mg tremelimumab for patients >30 kg will be administered using an IV bag containing 0.9% (w/v) saline, with a final tremelimumab concentration ranging from 0.1 mg/mL to 10 mg/mL, and delivered through an IV administration set with a 0.2 µm or 0.22 µm in-line filter. Remove 3.8 mL of IV solution from the IV bag prior to addition of tremelimumab. Next, 3.8 mL of tremelimumab (ie, 75 mg of tremelimumab) is added to the IV bag such that final concentration is within 0.1 mg/mL to 10 mg/mL (IV bag volumes 50 to 500 mL). Mix the bag by gently inverting to ensure homogeneity of the dose in the bag.

Patient weight at baseline should be used for dosing calculations unless there is a ≥10% change in weight. Dosing day weight can be used for dosing calculations instead of baseline weight per institutional standard.

For patients <30 kg, Calculate the dose volume for tremelimumab and number of vials needed for subject to achieve the accurate dose.

Tremelimumab will be administered at room temperature (approximately 25°C ) by controlled infusion via an infusion pump into a peripheral or central vein. Following preparation of tremelimumab, the entire contents of the IV bag should be administered as an IV infusion over approximately 60 minutes ( $\pm 5$  minutes), using a 0.2, or 0.22- $\mu$ m in-line filter. Less than 55 minutes is considered a deviation.

The IV line will be flushed with a volume of 0.9% (w/v) saline equal to the priming volume of the infusion set used after the contents of the IV bag are fully administered, or complete the infusion according to institutional policy to ensure the full dose is administered and document if the line was not flushed.

Standard infusion time is 1 hour. However, if there are interruptions during infusion, the total allowed time should not exceed 8 hours at room temperature. The table below summarizes time allowances and temperatures.

#### **Tremelimumab hold and infusion times**

|                                                              |                                                     |
|--------------------------------------------------------------|-----------------------------------------------------|
| Maximum time from needle puncture to start of administration | 4 hours at room temperature, 24 hours at 2°C to 8°C |
| Maximum time for IV bag infusion, including interruptions    | 8 hours at room temperature                         |

In the event that either preparation time or infusion time exceeds the time limits outlined in the table, a new dose must be prepared from new vials. Tremelimumab does not contain preservatives, and any unused portion must be discarded.

#### **5.2.4 Monitoring of dose administration**

Patients will be monitored during and after the infusion with assessment of vital signs at the times specified in the Study Protocol.

In the event of a  $\leq$ Grade 2 infusion-related reaction, the infusion rate of study drug may be decreased by 50% or interrupted until resolution of the event and re-initiated at 50% of the initial rate until completion of the infusion. For patients with a  $\leq$ Grade 2 infusion-related reaction, subsequent infusions may be administered at 50% of the initial rate. Acetaminophen and/or an antihistamine (eg, diphenhydramine) or equivalent medications per institutional standard may be administered at the discretion of the investigator. If the infusion-related reaction is  $\geq$ Grade 3 or higher in severity, study drug will be discontinued.

As with any antibody, allergic reactions to dose administration are possible. Appropriate drugs and medical equipment to treat acute anaphylactic reactions must be immediately available, and study personnel must be trained to recognize and treat anaphylaxis. The study site must have immediate access to emergency resuscitation teams and equipment in addition to the ability to admit patients to an intensive care unit if necessary

### **5.2.5 Accountability and dispensation**

General Accountabilities and each dispensation of durvalumab and tremelimumab should be recorded on the pharmacy drug accountability logs and patient accountability log of the study and should be kept in the pharmacy files. General accountabilities and dispensation of durvalumab to each subject (dose, lot number, dates etc..) will be verified by the clinical research associate during monitoring visit at the pharmacy.

### **5.2.6 Disposition of unused investigational study drug**

The site will account for all investigational study drug dispensed and also for appropriate destruction. Certificates of delivery and destruction must be signed and a destruction certificates should be provided and signed for each durvalumab destruction.

## **5.3 FOLFOX**

Tremelimumab will be administered first, then Durvalumab and then FOLFOX will be administered last and will be delivered as standard practice q2w.

### **5.3.1 Formulation/packaging/storage**

FOLFOX will be supplied by each site as this treatment is already on the market. Each investigational site will be provided by 5mg/mL Oxaliplatin vial (100mg/20mL); 50mg/mL 5-Fluorouracil vial (5000mg/100mL) and Folinic acid 200mg/mL for infusion after dilution. Oxaliplatin, Folinic acid and 5-Fluorouracil are stored between 15°C to 25°C and must not be frozen. Oxaliplatin and 5-Fluorouracil must be used within the individually assigned expiry date on the label.

### **5.3.2 Product preparation, Doses and treatment regimens administration**

Subjects will be administered with FOLFOX in line with normal clinical practice, with a dose and schedule of Oxaliplatin, 85 mg/m^2 administered as intravenous infusion over 2 hours in 250 ml dextrose 5% or sterile water for injection concurrently (via a Y-connector) with LV, 400 mg/m^2 (400 mg/m^2 for form dl or 200 mg/m^2 for form l) administered as intravenous infusion over 2 hours, in 250 ml dextrose 5%, or sterile water for injection followed by 5-FU, 400 mg/m^2 administered as a bolus injection (intravenous push administered manually in approximately 2 minutes), followed by 5-FU, 2400 mg/m^2 administered as a intravenous infusion over 46 hours. Oxaliplatin should always be administered before fluoropyrimidines.

Dose of oxaliplatin, 5-FU and LV will be administered on the basis of milligrams of each drug per square meter of body surface area (BSA) as measured at baseline (mg/m^2). The dose of oxaliplatin administered should be as close as possible to the calculated dose and will be limited to a maximum BSA of 2.0 m^2. Though the weight of the patient may change throughout the study, BSA will be assumed to stay close to that measured at baseline, i.e. no dose adjustments for changes in body weight will be done unless weight loss alone is considered to be an adverse event of grade 2 or more. Cycle length is 2 weeks comprising approximately 48 hours of infusion and 12 days of rest. It is expected that subjects will receive between 1 and 12 cycles of FOLFOX (6 months).

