**Figure 1a: Schedule of assessment for principal study – Association phase**

| Assessments to be performed
at the times stipulated in the
table and as clinically required
in the management of the subject | Scree-ning
(J-28 à J-1) | FOLFOX + Durvalumab (MEDI4736) +
Tremelimumab |    |    |    |    |    |    |    |
|---------------------------------------------------------------------------------------------------------------------------------------|----------------------------|--------------------------------------------------|----|----|----|----|----|----|----|
|                                                                                                                                       |                            | V1                                               | V2 | V3 | V4 | V5 | V6 | V7 | V8 |
|                                                                                                                                       |                            | Month                                            | M1 | M2 | M3 | M4 |    |    |    |
| Written informed consent/assignment of subject
identification number                                                               | X                          |                                                  |    |    |    |    |    |    |    |
| Demography and history of tobacco and alcohol use                                                                                     | X                          |                                                  |    |    |    |    |    |    |    |
| Previous treatments for colo-rectal cancer                                                                                            | X                          |                                                  |    |    |    |    |    |    |    |
| Verification of eligibility criteria                                                                                                  | X                          |                                                  |    |    |    |    |    |    |    |
| Inclusion of the subject                                                                                                              | X                          |                                                  |    |    |    |    |    |    |    |

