**Figure 1b: Schedule of assessment for principal study – Maintenance phase**

| Assessments to be performed
at the times stipulated in the
table and as clinically required
in the management of the subject | Durvalumab (MEDI4736) alone                 |     |     |     |     |     |     |     |     |     |     |     |     |     |     |     |     |     |     |     |     |     |     |     |
|---------------------------------------------------------------------------------------------------------------------------------------|---------------------------------------------|-----|-----|-----|-----|-----|-----|-----|-----|-----|-----|-----|-----|-----|-----|-----|-----|-----|-----|-----|-----|-----|-----|-----|
|                                                                                                                                       | V9                                          | V10 | V11 | V12 | V13 | V14 | V15 | V16 | V17 | V18 | V19 | V20 | V21 | V22 | V23 | V24 | V25 | V26 | V27 | V28 | V29 | V30 | V31 | V32 |
|                                                                                                                                       | M5                                          |     | M6  |     | M7  |     | M8  |     | M9  |     | M10 |     | M11 |     | M12 |     | M13 |     | M14 |     | M15 |     | M16 |     |
| Written informed consent/assignment of subject identification number                                                                  |                                             |     |     |     |     |     |     |     |     |     |     |     |     |     |     |     |     |     |     |     |     |     |     |     |
| Demography and history of tobacco and alcohol use                                                                                     |                                             |     |     |     |     |     |     |     |     |     |     |     |     |     |     |     |     |     |     |     |     |     |     |     |
| Previous treatments for colo-rectal cancer                                                                                            |                                             |     |     |     |     |     |     |     |     |     |     |     |     |     |     |     |     |     |     |     |     |     |     |     |

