## **5.2.2 Duration of treatment and criteria for retreatment**

**Treatment will be delivered with a maximum of 24 months:**

- 4 months with the association Durvalumab + Tremelimumab + FOLFOX (M1 to M4)
- 20 months of maintenance with Durvalumab alone (M5 to M24)

Retreatment is allowed (**once only**) for patients meeting the retreatment criteria below. The same treatment guidelines followed during the initial 24-month (4 months with the association + 20 months maintenance) treatment period will be followed during the retreatment period, including the same dose and frequency of treatments and the same schedule of assessments.

Patients may undergo retreatment in 1 clinical scenarios, described below:

1. Patients who complete the 4 dosing cycles of the combination of durvalumab and tremelimumab portion of the regimen (with clinical benefit per Investigator judgment), but subsequently have evidence of PD during the durvalumab monotherapy portion of the combination regimen, with or without confirmation according to RECIST 1.1, may restart treatment with the combination (FOLFOX + Durvalumab + Tremelimumab).

Before restarting their assigned treatment, the Investigator should ensure that the patient :

- does not have any significant, unacceptable, or irreversible toxicities that indicate continuing treatment will not further benefit the patient.
- Still fulfils the eligibility criteria for this study, to restart folfox, durvalumab and tremelimumab.
- Has not received an intervening systemic anticancer therapy after their assigned treatment discontinuation.
- Has to perform a baseline tumor assessment within 28 days of restarting their assigned treatment; all further scans should occur with the same frequency as during the initial 12 months of treatment (relative to the date of randomization) until study treatment is stopped (maximum of 12 months of further treatment).

During the retreatment period, patients receiving durvalumab + tremelimumab may resume durvalumab dosing at 750mg q2w with 75 mg of tremelimumab q4w for 4 doses each and combined to FOLFOX for 3 months. Patients will then continue with durvalumab monotherapy at 750 mg q2w, until month 24 if no PD is observed.

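### The protocol gives inconsistent lengths for the initial FOLFOX course: 6 cycles in Figure 1a, 4 months in section 5.2.2, up to 12 cycles in section 5.3.2

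*Protocol*

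**What the plan says.** The protocol describes the length of FOLFOX in five places.

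- **Figure 1a (association phase schedule).** The column heading over V1 to V8 begins "FOLFOX + Durvalumab (MEDI4736". In the row "FOLFOX administration", however, V1 to V6 are marked and V7 and V8 are blank. The durvalumab row above it is marked through V8, and tremelimumab is marked at V7.
- **Section 5.2.2, initial treatment.** "4 months with the association Durvalumab + Tremelimumab + FOLFOX (M1 to M4", followed by "20 months of maintenance with Durvalumab alone (M5 to M24". Figure 1b agrees on the second part: its heading from V9 is "Durvalumab (MEDI4736) alone" and its FOLFOX row is empty.
- **Section 5.2.2, retreatment.** The retreatment course is to follow the guidelines of the initial period, with the antibodies "combined to FOLFOX for 3 months".
- **Section 5.3.2.** "It is expected that subjects will receive between 1 and 12 cycles of FOLFOX (6 months". Retreatment is not mentioned there.
- **Section 6.2.2, laryngopharyngeal dysesthesia.** If oxaliplatin is stopped for neurotoxicity, the fluoropyrimidine continues for 3 or 6 months as set by randomization. The synopsis describes the trial as non-randomized.

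The interval is not in dispute. Section 5.2.1 says "FOLFOX will be administered last and will be delivered as standard practice q2w", and section 5.3.2 gives a two-week cycle.

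**The concern.** FOLFOX is the chemotherapy backbone of a single-arm, first-line regimen, so there is no control arm to absorb a difference in how long it is given. A site that follows the schedule stops after V6. One that follows section 5.2.2 could continue through month 4, and one that follows section 5.3.2 could continue through month 6. Each could claim to comply.

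Three things depend on the answer:

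- planned oxaliplatin exposure, and hence the cumulative toxicity to be expected, after month 3;
- what the median PFS and OS describe. Section 9.3 collects PFS at months 3 and 6, so the readings diverge inside that window;
- the per-protocol set in sections 11.2.2 and 11.3.2, which is defined by receipt of every planned dose. A patient given 6 FOLFOX cycles is complete by Figure 1a and short by the 4-month reading of section 5.2.2.

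**Working it through.** **Inputs.** FOLFOX every 2 weeks (sections 5.2.1 and 5.3.2); two visits per month, since V1 to V8 are M1 to M4 (Figure 1a); oxaliplatin 85 mg/m2 per cycle (section 5.3.2).

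**The plan's own figure.** Twelve cycles at 2 weeks is 12 × 2 = 24 weeks, or 6 months of 4 weeks. The statement in section 5.3.2 is consistent with itself.

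**Formulas.** Cycles = months × 4 / 2. Last planned dose at week 2 × (cycles − 1). Cumulative oxaliplatin = cycles × 85 mg/m2.

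| Source | Stated | Cycles | Last planned dose | Cumulative oxaliplatin |
|---|---|---|---|---|
| Figure 1a | 6 marks, V1–V6 | 6 (counted) | week 10 (V6) | 6 × 85 = 510 mg/m2 |
| Section 5.2.2, initial course | 4 months | 4 × 4 / 2 = 8 (inferred) | week 14 (V8) | 8 × 85 = 680 mg/m2 |
| Section 5.3.2 | up to 12 cycles, 6 months | 12 (printed) | week 22 (V12), if consecutive | 12 × 85 = 1020 mg/m2 |
| Section 5.2.2, retreatment | 3 months | 3 × 4 / 2 = 6 | not applicable | 510 mg/m2 |

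The range across readings of the initial course is 1020 / 510 = 2. With calendar months (months × 30.4375 / 14) the counts are 6.5 for 3 months, 8.7 for 4 and 13.0 for 6, so the choice of month does not close the gap.

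**Overlap with maintenance.** V9 falls at week 2 × (9 − 1) = 16, which is where sections 5.2.1 and 5.2.2 and Figure 1b all start durvalumab alone. Twelve consecutive cycles would place cycles 9 to 12 at V9 to V12, in M5 and M6, where Figure 1b leaves the FOLFOX row empty. V12 is also the second on-treatment CT.

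**Effect on the primary decision.** The primary objective is evaluated at 3 months, and the first on-treatment CT is at V6. All three readings give FOLFOX at V1 to V6, so planned exposure up to that scan is the same. The decision rule does not involve the number of cycles. With 16 then 27 patients, continuation at 9 or more and success at 26 or more of 43, the probability of success is the sum over x from 9 to 16 of P(X1 = x) × P(X2 ≥ 26 − x), where X1 ~ Bin(16, p) and X2 ~ Bin(27, p). This gives 0.093 at p = 0.50 and 0.901 at p = 0.707, in line with the stated 10% alpha and 90% power.

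**The case against.** The strongest defence is that the passages can be made to agree.

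- **The 4 months may only label a phase.** Tremelimumab is given four times, at V1, V3, V5 and V7, so the association phase lasts to M4 whatever FOLFOX does, and the FOLFOX row supplies the detail. This is a fair reading, and the 8 cycles are an inference rather than a printed number. But section 5.2.2 names FOLFOX within the 4 months, and nothing says that it stops before the phase ends.
- **The 3-month retreatment text supports the schedule.** It comes to 6 cycles, the same as Figure 1a. This stands: a reader might count it as a further conflict with the schedule, but it agrees with it.
- **The 12 may be 6 initial plus 6 retreatment cycles.** Retreatment is allowed once, and section 5.3.2 gives an expected range rather than a prescription. The sum is stated nowhere. It also works only if the initial course is 6 cycles, since 8 + 6 = 14 exceeds 12. It leaves 6 cycles against 4 months unresolved.
- **Section 8.1.2 sends sites to the schedule for treatment-phase procedures.** That gives Figure 1a some weight, but it does not say that the schedule overrides the FOLFOX dosing section.

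A reader might also infer that maintenance starts at three different times. It does not: Week 16, M5 and V9 are the same point, and only the end of chemotherapy varies. Another inference is that site is confounded with chemotherapy exposure. Nothing in the protocol shows sites following different passages, so this is conjecture.

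**Conclusion.** The inconsistency is real and unreconciled. Six cycles (Figure 1a, matched by the retreatment text) stand against a 4-month association (8 cycles, inferred) and an expectation of up to 12, with a leftover reference to a randomized duration. Planned cumulative oxaliplatin is 510, 680 or up to 1020 mg/m2. The 680 assumes that FOLFOX runs for the whole 4 months; the 1020 for an initial course assumes that the 12 cycles are consecutive. If the 4 months is only a phase label, 6 against up to 12 remains.

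The consequence is limited to what follows month 3: exposure and cumulative toxicity, the interpretation of median PFS and OS, and membership of the per-protocol set, which is a repeat analysis beside the primary modified ITT. It would be tempting to conclude that the 3-month go/no-go result is compromised. The protocol does not support that, because planned FOLFOX is the same through V6 under every reading and the error rates do not depend on the number of cycles.

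**What to change.** Reconcile Figure 1a, section 5.2.2 (initial and retreatment text), section 5.3.2 and section 6.2.2 to one stated maximum number of FOLFOX cycles for the initial course. State whether the 12 in section 5.3.2 includes retreatment, and remove the reference to randomization. Use the same number in the schedule and in the definition of planned doses for the per-protocol set. If FOLFOX is meant to end before the association phase does, say so in section 5.2.2. The choice of duration belongs to the sponsor and investigators; none is proposed here.

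In the report, tabulate FOLFOX cycles received per patient. The data are already collected, since section 5.3.4 requires patient-level accountability logs. The cost is amendment wording and one exposure table.
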